### Termination of participation

Patient participation in the study may terminate for reasons such as withdrawal of informed consent, ineligibility (screening failure), failure to commence treatment within this registry, loss to follow-up, death and termination of participation by the sponsor. Detailed information explaining the circumstances leading to the termination will be recorded in a dropout form. For these patients, the collected data will be censored as the day of termination and may be used in the analysis.

### Outcome measures

Clinical and functional outcomes, radiological outcomes and patient-reported outcomes (PROs) will be collected according to the schedule outlined in table 2.

#### Clinical and functional outcomes

The following will be documented:

Condition of the eyelid and palpebral border.Condition of the globe such as its position, existence of anisocoria and/or strabismus and entrapment/impingement.Extraocular motility assessed by ‘follow my finger test’ in eight directions.Diplopia quantified by measuring the field of single binocular vision, ranging from 0 to 3:0: no diplopia.1: mild (diplopia appears more than 30 degrees from the primary position).2: moderate (diplopia appears between 10 and 30 degrees from the primary position).3: severe (diplopia appears within 10 degrees from the primary position).Vision: visual acuity will be measured using a visual test chart for both healthy and injured side with and without vision aids (as applicable) and expressed as percentage of visus.Sensory disturbances on the second branch of the fifth cranial nerve: anaesthesia, paraesthesia, hypoaesthesia or hyperaesthesia.

#### Radiological outcomes

The following will be measured centrally by one expert as described by Schouman *et al*^25^ using the collected images:

Pre-treatment parameters

Degree of displacement of the fracture.Position of the inferior rectus muscle relative to the bone fragments.Shape of the inferior rectus muscle.Orbital volume of the injured compared with the uninjured side.Maximal height or periorbital tissue herniation.

Post-treatment parameters

Orbital volume of the reconstructed compared with the uninjured side.

#### Patient-reported outcomes

The PROs used in this study are the Diplopia Questionnaire (DQ), the self-reported perception of visual acuity, strabismus and symmetry, and the AO CMF Injury Symptom Battery questionnaire.

DQ consists of seven questions concerning double vision in seven different gaze positions. It has been validated for responsiveness and test-retest reliability and has been shown to have good psychometric characteristics.^26^ The self-reported perception of visual acuity, strabismus and symmetry asks patients to evaluate on a 5-point Likert scale.

The AO CMF Injury Symptom Battery is the first PRO instrument developed specifically for traumatic craniomaxillofacial injuries with four modules specific to the injury site (oral, ocular, nasopharyngeal, ear) and five universal modules (pain/sensation, cognitive, cosmetic, psychosocial and injury impact).^27^ The items in this instrument were codeveloped by experts and patients and cognitive debriefing interviews were conducted with patients to assess the appropriateness and comprehensibility of the items.^27^ In the current registry, the ocular and psychosocial modules were used consisting of eye problems (7 items) and psychosocial problems (12 items). The questionnaire is available in English only and will be used only in English-speaking sites. The psychometric properties of this instrument have not been validated.

### Adverse Events

As this is an observational study, only anticipated condition-related, treatment-related or implant-related adverse events (AE) will be recorded from the time of consent onwards. These include AEs that are hardware-related (eg, malpositioning, extrusion, breakage or loosening of the implant), related to soft tissues (eg, infection, extraocular muscle entrapment, bleeding complications, persistent pain), related to the globe and vision (eg, globe dislocation, sclera show, epiphora, loss of vision), neurological-related (eg, mydriasis, optic nerve injury, infraorbital numbness, extraocular muscle palsy) and any other AE related to the OFx or OFx treatment.

Each AE will be followed up until resolved with or without persistent damage or until the end of the patient’s study participation, whichever occurs first. Unless it is indicated by the local EC/IRB, immediate reporting of AEs to the local EC/IRB is not required in this registry.

This registry can be considered as a minimal risk study given that participation does not pose additional risk as compared with the standard of care procedures.

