##### Follow-up schedule

In general, patients will be followed up counting from Day 0 at approximately 6 weeks, 3 months and 6 months, as conforming to the routine visit schedule at the study site. These patients will remain active in the study for 6 months unless they received additional treatments.

The definition of ‘Day 0’ is different for different patients. For patients with acute fractures, if the patient:

is treated non-surgically, Day 0 is the day of the diagnosis.is treated with primary ‘early’ or ‘delayed’ reconstruction, Day 0 is the day of the surgery.is treated with secondary reconstruction within the registry but had a primary reconstruction prior to enrolment, Day 0 is the day of the first surgery performed within this registry.is treated with primary reconstruction within the registry but then requires secondary reconstruction, Day 0 remains the day of the primary reconstruction and will not be shifted. The patients will be followed up at approximately 6 months after the secondary reconstruction according to the site’s routine visit schedule. These patients will remain active in the study for 6 months from the secondary reconstruction or up to the maximum of 1 year since Day 0.For patients needing more than one surgery within this study, they will remain active in the registry for 6 months after the last surgery but with the limit of maximally 1 year counting from Day 0.

The schedule for data collection at each visit is summarised in table 2.

**Table 2 T2:** Schedule of follow-up visits and data collection

	Baseline	Treatment	Post-treatment visit 1	Post-treatment visit 2	Post-treatment visit 3	Additional treatment
	–	Day 0	6 weeks (+14 days)	3 months (+14 days)	6 months (+14 days)	Any time during follow-up
Eligibility	X					
Patient information/consent	X*					
Demographics and medical history	X					
Injury details	X					
Treatment details		X†				X
Clinical and functional outcomes	X‡		X	X	X	
Patient-reported outcomes	X§		X	X	X	
Adverse events/complications	X	X	X	X	X	X
Images (eg, CT, CBCT, X-rays)	X¶	X¶	X¶	X¶	X¶	X¶

* Informed consent may occur after treatment under certain circumstances (eg, treatment is immediate emergency, patient has temporarily impaired decision-making capacity, patient is unable to give written consent due to their injuries). No data can be collected in the eCRF prior to consent.

† For patients who undergo primary ‘delayed’ surgery, the Day 0 is considered as the day of the surgery.

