‡ Clinical and functional outcomes at baseline refer to the status post injury and prior to treatment.

§ Patient-reported outcomes at baseline refer to the status post injury and prior to treatment.

¶ Only images (CT, CBCT, X-ray, etc) taken as part of the standard of care procedures will be collected. All images and pictures are de-identified.

CBCT, cone beam CT.

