### Statistical analysis

This is a registry-style observational study that aims to increase our knowledge about the treatment and outcome of OFx. Therefore, there is no formal statistical hypothesis and no formal sample size calculation. However, a detailed statistical analysis plan will be prepared before the final analysis documenting the descriptive statistics to be used for data assessment.

As the aim of the current registry is mainly descriptive, the patient characteristics, clinical data and outcomes recorded at routine standard of care scheduled follow-up assessments will be presented using simple summary statistics. Categorical variables will be summarised using the frequency and percentage for each category. Continuous variables will be summarised using the mean, SD, median, IQR, and minimum and maximum. Additionally, these summary statistics will be presented according to clinically relevant categories, for example, according to treatment received (conservative vs surgical treatment). Depending on the volume and the quality of the collected data, further appropriate statistics will be applied.

The AEs will be summarised both at patient level and AE level. AE rates with 95% CIs will be calculated based on the total population size, irrespective of dropouts during follow-up.

In general, all enrolled and eligible patients who were treated within the registry will be included in the analysis. If a patient discontinues participation due to any reason, all data collected before discontinuation will be integrated into the analysis. For specific research questions, only certain subgroups of patients may be relevant. In such a case, prior to the analysis, it will be defined which patients will be included in the analysis. Details concerning the handling of missing data and protocol violations will be specified in the statistical analysis plan.

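### Adverse events are recorded only from consent, but consent may follow treatment, so peri-operative events that resolve before a late consent go uncounted while the patient stays in the denominator

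*Protocol article*

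**What the plan says.** Four statements in the protocol article bear on this.

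- **Start of recording** (Adverse Events): "only anticipated condition-related, treatment-related or implant-related adverse events (AE) will be recorded from the time of consent onwards".
- **Timing of consent** (Follow-up schedule, Table 2 footnote): "Informed consent may occur after treatment under certain circumstances". The examples are emergency treatment, temporarily impaired capacity, and injuries that prevent written consent. The footnote adds: "No data can be collected in the eCRF prior to consent".
- **Visit schedule** (Table 2): the row "Adverse events/complications" is marked at Baseline, Treatment (Day 0), all three follow-up visits and any additional treatment. It carries no footnote for patients consented late.
- **Denominator** (Statistical analysis): adverse event rates with 95% confidence intervals are "calculated based on the total population size", whether or not patients later drop out.

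For primary surgical patients, the Follow-up schedule sets the time origin at the operation: "is treated with primary ‘early’ or ‘delayed’ reconstruction, Day 0 is the day of the surgery".

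**The concern.** Follow-up of an operated patient is counted from the operation, but safety recording is counted from a signature. The two usually cause no conflict because consent comes first. In the patients the footnote describes, consent comes second, and the interval between operation and consent is when intra-operative and early post-operative events occur. On the wording of the Adverse Events section that interval is outside the recording window. The patient still counts as one of the persons at risk.

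The missing events are not a random subset. They belong to patients treated urgently or unable to consent. The article's second objective is to describe and compare surgical and non-surgical outcomes, and an undercount of peri-operative events affects only the surgical side. This is a data-collection rule: an analysis plan can set aside events recorded at the wrong time, but it cannot restore events that were never recorded.

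**Working it through.** There is no stated adverse event rate or sample size calculation to reproduce. The check consists of setting the rules side by side and following patients through them.

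**1. Following a surgical patient through the rules.** Let the operation be at Day 0, consent at day *c*, and an adverse event start at day *t* and resolve at day *r*.

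- *Consent before or on Day 0.* Every event from the operation onwards lies inside the window. The Table 2 mark at Treatment can be met.
- *Consent after Day 0, event starts after consent (t ≥ c).* Recorded.
- *Consent after Day 0, event starts before consent and is still present at consent (t < c < r).* Unclear. It could be picked up, but the article does not say.
- *Consent after Day 0, event starts and resolves before consent (r < c).* Outside the window and not recorded. The Table 2 mark at Treatment cannot be met under the Adverse Events rule.

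In all four cases the patient is in the denominator. The last case therefore contributes to the denominator and not to the numerator.

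**2. What the shortfall depends on.** Among operated patients, let *p* be the true proportion with at least one listed event from Day 0, *f* the share of those event patients who were consented after treatment, and *s* the share of that late-consented subset whose events all lie wholly before consent. Then

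recorded proportion = p × (1 − f × s), shortfall = p × f × s.

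The shortfall is zero if nobody is consented late (*f* = 0) or if no event resolves before consent (*s* = 0), and it cannot exceed *p* × *f*. If risk does not depend on consent timing, *f* equals the share of operated patients consented late; if emergency cases carry more risk, *f* is larger than that share.

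The article gives none of *p*, *f* or *s*. It says only that late consent arises under certain circumstances. Any percentage for the bias would be the product of three guesses, so none is given here. The one available scale is the planned enrolment of about 300: each patient whose only events are missed lowers the overall patient-level rate by 1/300, or 0.33 percentage points. It lowers a surgical-only rate by more, because that denominator is smaller. This is a unit of measurement and not an estimate of the loss.

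The article also plans an event-level summary. There a missed event is lost even if the same patient has another event recorded later.

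**3. Whether the consent rule forces the loss.** It does not. The Recruitment section and the Table 2 footnote bar entry into the electronic case report form before consent. They do not bar retrospective entry once consent exists. The Injury details and Treatment details sections already ask for retrospective documentation of injury and primary treatment when reconstruction took place before enrolment. Retrospective entry of adverse events would follow the same pattern.

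**The case against.** **The phrase may describe when recording starts, not event onset.** On that reading, staff begin filling in the form at consent and may enter earlier events, so nothing is lost. This is possible, and the Treatment mark in Table 2 favours it. But the article does not say so, the more natural reading is onset, and two sites could follow the text and record the same patient differently. The wording needs repair on either reading.

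**Late consent is exceptional and the registry is descriptive.** Both are true. There is no formal hypothesis, and the effect may be small. This limits the severity and does not remove the selective direction of the loss.

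**A fuller protocol or form guidance may settle it.** It may. The article does not leave the starting point open, however; it fixes it at consent.

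A reader might infer three stronger points, none of which the article supports.

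- *Presenting injury signs inflate the rates in everyone else.* Entrapment, mydriasis and infraorbital numbness are on the adverse event list and resemble presenting signs. But the onset reading that loses peri-operative events also excludes signs that began at injury, before consent. The reading that lets those signs in also lets the earlier events in. Both problems cannot be claimed at once. Presenting status also has its own Baseline row in Table 2, and non-surgical patients, whose Day 0 is the day of diagnosis, have essentially no window between consent and Day 0.
- *Patient-reported change scores mix real and recalled baselines.* The footnote says "Patient-reported outcomes at baseline refer to the status post injury and prior to treatment". Nothing says that late-consented patients supply a recalled value; it could simply be missing. No change-from-baseline analysis is described.
- *A numerical bias can be quoted.* It cannot, for the reasons given in the working.

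One further objection to a simple remedy does stand. Opening the window only at Day 0 would discard new events arising between consent and surgery, an interval that can exceed three weeks in delayed cases. The fix has to keep these.

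**Conclusion.** The point holds in a narrow form. The Adverse Events section and Table 2 with its consent footnote cannot both be followed for a patient consented after surgery. On the plain reading, events that start and resolve between operation and late consent are never counted, while the patient remains in the denominator. Surgical adverse event rates are then understated, selectively in urgent or impaired patients. The direction is clear; the size is unknown, because the share consented late, the event rate and the time from operation to consent are not given. The conclusion rests on reading the consent clause as referring to event onset, and on sites not already entering earlier events retrospectively. It should be corrected, because the omission arises at collection, but it does not threaten the registry as a whole.

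**What to change.** Reconcile the Adverse Events section with Table 2 as follows.

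1. Record listed adverse events from Day 0 or consent, whichever is earlier, each with an onset date.
2. For patients consented after treatment, enter events since Day 0 retrospectively from the chart once consent has been given, subject to local ethics approval. Add a footnote to this effect on the adverse event row of Table 2.
3. Base the surgical and non-surgical adverse event rates on events with onset or worsening after Day 0.
4. Report events between consent and Day 0 separately, so that they are kept without entering the comparison.

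The cost is a revised paragraph and footnote, form guidance on onset dates, matching wording in the analysis plan, and some chart look-back for late-consented patients. Transient events that were never charted will remain missing, so the number of patients consented after treatment should be reported beside the rates. No data would be entered before consent.

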### Statistical analysis

This is a registry-style observational study that aims to increase our knowledge about the treatment and outcome of OFx. Therefore, there is no formal statistical hypothesis and no formal sample size calculation. However, a detailed statistical analysis plan will be prepared before the final analysis documenting the descriptive statistics to be used for data assessment.

As the aim of the current registry is mainly descriptive, the patient characteristics, clinical data and outcomes recorded at routine standard of care scheduled follow-up assessments will be presented using simple summary statistics. Categorical variables will be summarised using the frequency and percentage for each category. Continuous variables will be summarised using the mean, SD, median, IQR, and minimum and maximum. Additionally, these summary statistics will be presented according to clinically relevant categories, for example, according to treatment received (conservative vs surgical treatment). Depending on the volume and the quality of the collected data, further appropriate statistics will be applied.

The AEs will be summarised both at patient level and AE level. AE rates with 95% CIs will be calculated based on the total population size, irrespective of dropouts during follow-up.

In general, all enrolled and eligible patients who were treated within the registry will be included in the analysis. If a patient discontinues participation due to any reason, all data collected before discontinuation will be integrated into the analysis. For specific research questions, only certain subgroups of patients may be relevant. In such a case, prior to the analysis, it will be defined which patients will be included in the analysis. Details concerning the handling of missing data and protocol violations will be specified in the statistical analysis plan.

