#### Recruitment

The recruitment period will be ~36 months, during which approximately 300 patients are planned to be enrolled.

The participating sites will identify all consecutive eligible patients according to the defined inclusion and exclusion criteria. Eligibility assessment will be performed by the investigator and/or adequately trained member(s) of the research team. The assessment of eligibility includes but is not limited to an inquiry about the interest and willingness of the patient to participate in the research project. Data collection for this registry is not allowed without the consent of the patient or surrogate, and therefore, no data are collected in the electronic case report form (eCRF) prior to obtaining consent by the patient.

All consented patients will be allocated to a unique patient number. Each site will keep an Identification List linking the patient number with his/her personal information. Such Identification List is kept safe and in a locked place always. Sites are not allowed to share the Identification List with any third party except for the sponsor representative, legal authorities and EC/IRB, who may have access to the Identification List during monitoring/auditing activities performed on-site.

All consented patients should be followed up within the registry, except if their study participation is prematurely terminated.

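### Dividing AE counts by the total population irrespective of dropout understates 6-month complication risk, and the denominator for hardware AEs is left unclear

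*Protocol article*

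**What the plan says.** All places are in the Protocol article.

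- **Statistical analysis:** "AE rates with 95% CIs will be calculated based on the total population size, irrespective of dropouts during follow-up". AEs are to be summarised per patient and per event. The interval method is not named. The analysis set is given as "all enrolled and eligible patients who were treated within the registry will be included in the analysis". The preceding paragraph plans summary statistics broken down by the treatment the patient received, and missing-data handling is left to the SAP.
- **Termination of participation:** for patients who leave early, "the collected data will be censored as the day of termination and may be used in the analysis".
- **Follow-up schedule:** standard follow-up is 6 months from Day 0. For patients with more than one surgery, "they will remain active in the registry for 6 months after the last surgery but with the limit of maximally 1 year", counted from Day 0.
- **Adverse Events:** AEs are recorded from consent onwards, and a footnote to the visit schedule allows consent after treatment in some circumstances. The listed AEs include those that are "hardware-related (eg, malpositioning, extrusion, breakage or loosening of the implant").
- **Objectives:** the second objective includes comparing outcomes between surgical and non-surgical treatment.
- **Sample size:** "approximately 300 patients are planned to be enrolled", and "there is no formal statistical hypothesis and no formal sample size calculation".

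**The concern.** A rate with a 95% CI will be read as an estimate of complication risk. With the total population as denominator, a patient who leaves at week 2 without an AE contributes the same as one observed AE-free for 6 months. The numerator loses the events that would have occurred after dropout, while the denominator loses nobody. The estimate falls, and the interval is computed as if everyone had been fully observed.

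The effect depends on how many patients leave, so it need not be equal in the two treatment groups. Follow-up follows each site's routine practice, and equal retention cannot be presumed. If retention differs, the rule can produce a difference in AE rates where none exists, in a registry that intends to compare the two groups.

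A second question is which patients make up the total population. Patients without an implant cannot have an implant extrusion or breakage. If they are counted for hardware AEs, the rate is diluted.

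**Working it through.** The plan gives no AE rate, dropout rate or surgical share, so it has no figure to reproduce. From the documents: N of about 300, 95% intervals, 6-month follow-up, and up to 12 months for re-operated patients. Assumed: true 6-month risk p, 6-month dropout d, share s followed to 12 months, and surgical share. A Wald interval is assumed for the crude rate.

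**1. Dropout, constant independent hazards.** With time in units of 6 months, λ = -ln(1-p) and μ = -ln(1-d):

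crude rate = λ/(λ+μ) × [1 - exp(-(λ+μ))]

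Example, p = 10%, d = 20%: λ = 0.1054, μ = 0.2231, sum 0.3285. Crude = 0.3207 × (1 - 0.72) = 0.0898.

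Crude half-width = 1.96 × √[0.0898 × 0.9102/300] = 3.2 points. The Kaplan-Meier (Greenwood) half-width is 1.96 × (1-p) × √{λ[exp(λ+μ) - 1]/[(λ+μ)N]} = 1.96 × 0.9 × √(0.3207 × 0.3889/300) = 3.6 points.

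Results for p = 10%, N = 300 (coverage by normal approximation):

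| Dropout | Crude rate | Relative bias | Half-width, crude vs Kaplan-Meier (points) | Ratio | Coverage of true risk |
|---|---|---|---|---|---|
| 10% | 9.5% | -5% | 3.3 vs 3.5 | 0.95 | 94.0% |
| 20% | 9.0% | -10% | 3.2 vs 3.6 | 0.90 | 90.5% |
| 30% | 8.4% | -16% | 3.2 vs 3.7 | 0.84 | 83.6% |
| 40% | 7.9% | -21% | 3.1 vs 3.9 | 0.78 | 72.1% |

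At p = 20% the crude rates are 19.0%, 18.0%, 16.9% and 15.8%. At 20% dropout, coverage is 85%.

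**2. Sensitivity to timing.** If 80% of AEs occur before any dropout and the rest follow constant hazards, p = 10% reads 9.9%, 9.8%, 9.7% and 9.6% for 10% to 40% dropout, a relative bias of -1% to -4%. At the other extreme, all dropout precedes any AE and the crude rate is p(1-d): 10% becomes 8% at 20% dropout.

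**3. Unequal dropout.** With a true risk of 20% in both groups and dropout of 10% in one and 30% in the other, the rule reports 19.0% and 16.9%. The 2.1-point difference is an artefact.

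**4. Extended follow-up.** With c6 the crude rate from step 1 and c12 the same formula over two units of time, the mixture is (1-s) × c6 + s × c12. At p = 10% and no dropout, following 5%, 10% or 20% of patients to 12 months raises the crude rate above the 6-month risk by 4.5%, 9% or 18% in relative terms. With 10% extended, the net is +2.7% at 10% dropout and -3.7% at 20% dropout.

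**5. Hardware AEs, only if the total population includes patients without an implant.** Suppose 150 of 300 have an implant and 15 of them (10%) have a hardware AE. On implanted patients: 15/150 = 10% (Wilson 95% CI 6.2% to 15.8%). On everyone: 15/300 = 5% (3.1% to 8.1%). With implanted shares of 30%, 70% and 90%, a true 10% reads 3%, 7% and 9%.

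**The case against.** The strongest reply is that x/N is a correct description of how many patients had a recorded AE, that it is openly stated, and that the registry is mainly descriptive with no hypothesis. This holds, and the crude figure should stay. It does not cover a figure that is called a rate, carries a 95% CI and may feed a comparison of treatment groups. Nor is the matter simply deferred: missing data are left to the SAP, but the AE denominator is settled in the article.

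Other objections stand and limit the point:

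- A reader might infer that AE rates ignore treatment. The text does not say so, and breakdowns by treatment received are planned. Whether AE rates then use the group size is unclear, so step 5 shows what a literal reading would do, not what the plan establishes.
- A reader might infer that ignoring follow-up length also biases rates low. Step 4 shows that it works the other way, so an overall downward bias is not established. Only the dropout component has a fixed direction.
- A reader might infer that binomial intervals will be put on event counts with several AEs per patient. No interval method is stated, so that is not supported.
- The termination text is not a flat contradiction. It can mean only that data collection stops on that day. The AE rule simply makes no use of the censoring.
- Several listed AEs, such as malpositioning or bleeding, could plausibly occur early, which favours the small bias in step 2.

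**Conclusion.** The point holds in limited form. As an estimate of 6-month complication risk, the stated rule counts patients lost early as AE-free. Its dropout component is therefore biased low, and its intervals are 5% to 22% narrower than a censoring-adjusted interval at 10% risk and 10% to 40% dropout. Under constant hazards the relative bias is about -5% to -21%; with 80% of AEs before dropout it is -1% to -4%. Every one of these figures rests on assumed AE and dropout rates, and low dropout would make the problem negligible. The consequence that matters most is a distorted surgical versus non-surgical comparison if dropout differs. The hardware-AE denominator is an ambiguity to close, not a demonstrated error. Severity: moderate.

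**What to change.** In the Statistical analysis section, or in the SAP with a matching protocol clarification:

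1. Keep n/N, but label it crude observed incidence.
2. State that denominators are the number of patients per treatment group and, for hardware AEs, the patients with an implant. Say how an implant placed before enrolment is counted.
3. Add a patient-level 6-month cumulative incidence from Day 0, by treatment group, with 95% CI. Censor at termination, and at 6 months so that the longer follow-up of re-operated patients does not mix exposure windows. Treat death, one of the listed termination reasons, as a competing event.
4. Because AEs are recorded only from consent, let patients enter the risk set at consent where consent follows Day 0.

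Item 3 needs AE onset dates. The article does not state that these are recorded, so this should be checked in the case report form first. The cost is a paragraph of wording and slightly more analysis. Where dropout is material, the added estimates will tend to be somewhat higher than the crude rates, with wider intervals. With the initial analysis expected by mid-2026, the change should be fixed before the data are analysed.
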